#### 4.2.4 TREATMENT COSTS AND BENEFITS

A health economic analysis will be integrated into the trial. Details of the health economic analysis will be detailed in a separate analysis plan. Mixed effects models will be used to analyse the health economic measures in the same way as the clinical measures.

#### 4.3 COVARIATE ADJUSTMENT AND POPULATION

All secondary analyses will account for GP practice as per the primary outcome. These analyses will be carried out on the ITT population.

#### 4.4 HANDLING MISSING DATA

Data will be analysed using an intention to treat analysis. All randomised patients will be included in the primary analysis up to the last follow-up or primary outcome event as appropriate, assuming non-informative censoring for those withdrawn from the study and not consenting to continued follow-up or those lost to follow-up.

All baseline covariates are expected to be observed. Baseline values will be summarised for those who did and did not complete follow up measurements, separately for those who withdrew completely from the study or were lost to follow-up and those who were withdrawn from medication but consented to further follow-up, in order to assess which observed characteristics are related to missingness. In the unlikely event that there is missing data at baseline then these will be imputed using a suitable method (for example a simple method such as mean imputation if the proportion of missing data is small, i.e. <10%, or the more sophisticated method of multiple imputation if there are substantial missing data at baseline).

For the secondary outcomes mixed models can account for missing data in the outcome at different time points so long as the outcome is observed at least one time point. Although time points for the main comparisons are as specified, all time points at which an outcome is measured will be included in the analysis model in order to aid with estimation in the presence of missing data. This analysis is valid under the missing at random (MAR) assumption, i.e. that the probability of a value being missing depends only on variables included in the model. The missing at random assumption will be tested for each secondary outcome as far as is possible by analysing each baseline covariate in a logistic regression model to determine which if any are associated with missingness (where the outcome is presence/absence of the outcome at the primary endpoint). Should any baseline clinical or demographic variable be predictive of later dropout this variable will be included as an additional covariate in the analysis, in order to ensure the MAR assumption is valid.

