#### **12.8. Procedure for Accounting for Missing, Unused, and Spurious Data.**

The missing at random assumption will be tested as far as is possible by analysing each baseline covariate in a regression model to determine which if any are associated with missingness.

All baseline covariates are expected to be observed. Baseline values will be summarised for those who did

and did not complete follow up measurements to describe any characteristics related to missingness that are able to be observed.

We will be analysing our data using an intention to treat analysis. All randomised patients will be included in the analysis, assuming non-informative censoring for those withdrawn from the study or lost to follow-up for the primary analysis.

During statistical data review and analysis, any anomalies in the data will be investigated and discussed with the trial management team. The data investigation will be broad and flexible and focus on variability of the data, consistency, dispersion, outliers, inliers, relationships between variables and relationships over time. The statistical data review will be fully documented with all the output dated. If fraud is proved, fraudulent data will be removed from the analysis.

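### Regressing missingness on baseline covariates cannot test or secure missing at random, and no sensitivity analysis departs from that assumption for eGFR, systolic blood pressure or ACR

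*Combined protocol and SAP*

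**What the plan says.** SAP 4.4 rests the secondary mixed models on MAR: "This analysis is valid under the missing at random (MAR) assumption". It defines MAR as missingness that depends only on variables in the model. It then sets out three steps.

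- **The check.** "The missing at random assumption will be tested for each secondary outcome as far as is possible by analysing each baseline covariate". This is a logistic regression, "where the outcome is presence/absence of the outcome at the primary endpoint". No visit is named, and the trial's primary endpoint is a time to event.
- **The action.** "Should any baseline clinical or demographic variable be predictive of later dropout this variable will be included as an additional covariate in the analysis". No threshold for being predictive is given.
- **What the action achieves.** It is taken "in order to ensure the MAR assumption is valid".

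Protocol 12.8 has the same check: "The missing at random assumption will be tested as far as is possible by analysing each baseline covariate in a regression model".

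The SAP also gives the models some protection: "all time points at which an outcome is measured will be included in the analysis model in order to aid with estimation". SAP 4.2.2 and 4.2.3 adjust systolic pressure and eGFR for baseline and fit all visits. For ACR, SAP 4.2.3 analyses only the change to the final visit.

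The planned sensitivity analyses are covariate adjustment of the primary outcome (SAP 6.1) and exclusion of outliers (SAP 4.5). Neither departs from MAR for a secondary outcome.

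**The concern.** Whether MAR holds turns on how missingness relates to the unobserved values, once the observed data are taken into account. A regression of missingness on baseline covariates contains no unobserved values, so neither a positive nor a negative result bears on that question. The qualifier about doing this as far as possible softens the claim to test MAR. It does not soften the claim that adding covariates ensures MAR.

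The trial is open label, and only one arm has trial treatment to stop. Loss of data could therefore differ between arms in ways linked to how participants are doing. If it did, the 3-year eGFR, systolic pressure and ACR differences would be reported as valid under MAR, with nothing to show how far they depend on it.

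**Working it through.** **The logic.** Let R = 1 if the 3-year value is missing, X the baseline covariates, A the arm, and Y(obs) and Y(mis) the observed and missing outcome values.

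- MCAR: P(R=1 | X, A, Y(obs), Y(mis)) = P(R=1).
- MAR: P(R=1 | X, A, Y(obs), Y(mis)) = P(R=1 | X, A, Y(obs)).
- The check fits logit P(R=1) = a + b·X(k), one covariate at a time, and looks at whether b = 0.

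A non-zero b contradicts MCAR but is compatible with MAR. A zero b does not imply MAR, because dependence on Y(mis) never enters the fit. As specified, arm and earlier post-baseline values do not enter either.

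**Simulation inputs.** The documents give no figure on this point, so there is none to reproduce. The following illustrates the logic for eGFR only.

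- Arm sizes: 677 and 695 (Supplementary Table 2).
- Control-arm dropout by 3 years: about 10% (protocol 12.3, overall attrition), or about 27% (SAP 2.4, 10% a year: 1 − 0.9³ = 0.271).
- Assumed: baseline eGFR SD 6; between-person and residual SD 4 each; decline of 1 ml/min/1.73m² a year; visits at 0.5, 1, 2 and 3 years; true treatment effect zero.
- Assumed dropout slopes per ml/min lower eGFR: log-odds 0.20 on the deviation from the value expected given baseline, or 0.12 on the eGFR level. The deviation has SD √(4² + 4²) = 5.66, so the first slope is an odds ratio of exp(0.20 × 5.66) = 3.1 per SD, which is strong.
- Model: random intercept per participant, with time, arm, time × arm and baseline eGFR. The practice effect was omitted and flagged covariates were not added. There were 500 trials per scenario, and a 5% threshold was assumed for the check.

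**Results.** Bias is in the 3-year difference, in ml/min/1.73m² (Monte Carlo standard error about 0.015). Each cell gives the lower, then the higher dropout setting.

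| Dropout mechanism | Missing at 3 years, spironolactone v control | Bias | False-positive rate | Check flags baseline eGFR |
|---|---|---|---|---|
| 1. MCAR | 9.8% v 9.9%; 27.1% v 27.1% | −0.01; 0.00 | 5.6%; 5.8% | 6%; 4% |
| 2. MAR, last observed level, treated arm only | 13.2% v 9.8%; 31.9% v 27.1% | −0.02; −0.01 | 5.8%; 6.0% | 96%; 99% |
| 3. MNAR, unseen deviation, treated arm only | 15.5% v 9.8%; 34.9% v 27.0% | +0.32; +0.75 | 16.0%; 58.6% | 5%; 4% |
| 4. MNAR, unseen deviation, both arms alike | 15.4% v 15.5%; 34.9% v 35.0% | 0.00; 0.00 | 5.2%; 4.4% | 4%; 5% |
| 5. MNAR, unseen level, treated arm only | 13.2% v 9.9%; 31.9% v 27.1% | +0.15; +0.41 | 8.8%; 21.4% | 96%; 100% |

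- Rows 1 and 3: the check behaves alike whether there is no bias or substantial bias.
- Rows 2 and 5: it fires in almost every trial, in one case with an essentially unbiased model and in the other with a biased one. Baseline eGFR is already in the model, so in row 5 the stated remedy would add nothing for it and the bias stays.
- Row 4: MNAR dropout acting alike in both arms leaves the contrast unbiased.
- In every scenario at least one of four irrelevant covariates was flagged in 17% to 21% of trials, as chance predicts (1 − 0.95⁴ = 18.5%).

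**ACR.** Protocol Appendix B and SAP Appendix II schedule urine ACR at baseline and week 156 only. Someone without the final value has no intermediate ACR for the model to use. SAP Appendix III marks ACR at every visit, which conflicts with those schedules.

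**The case against.** There is a good deal to be said for the plan.

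- **On the SAP's own definition the step is coherent.** If MAR means dependence only on variables in the model, an omitted covariate that predicts missingness shows the model to be incomplete, and adding it is reasonable. This stands for observed covariates. It does not reach unobserved outcome values.
- **The mixed model does much of the work.** Renal profile and office blood pressure are scheduled at all 15 follow-up visits, so much of a decline would be seen before dropout. Row 2 shows such dropout is handled. Using four visits probably overstates the bias. The protection does not extend to ACR.
- **Stopping treatment is not leaving follow-up.** Protocol 9.8 and 12.4 and SAP 3.4 keep treatment-stoppers in follow-up and analysis where possible, and SAP 4.4 summarises them separately. This largely stands, although protocol 11.4 and SAP 8.5 call for an end-of-study assessment after removal for an adverse event and do not say whether visits then continue.
- **The consequence is limited.** SAP 4.7 calls the secondary outcomes exploratory. A bias of 0.15 to 0.75 is small beside the 25% eGFR fall in SAP 2.2.3.2, which is 7.5 to 12.5 at eGFR 30 to 50. That threshold applies to individuals, however, not to a mean difference.

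A reader might infer that covariates are picked by P-value by unblinded statisticians who could steer the result. The documents do not support this. The statisticians are unblinded (SAP 2.5), but no threshold is stated and selection is on missingness, not on the treatment effect.

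**Conclusion.** The point holds as a matter of logic. The check cannot tell MAR from MNAR, adding baseline covariates cannot ensure MAR, and no planned analysis shows how sensitive the eGFR, systolic pressure or ACR comparisons are to a departure from it. The logic needs no assumed figures.

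The size does. Under arm-specific MNAR dropout the simulated eGFR bias ran from 0.15 to 0.75 ml/min/1.73m², with false-positive rates of 9% to 59%. These depend on the assumed SDs, slopes and visit pattern. The direction follows from assuming that treated participants with low eGFR drop out. Systolic pressure and ACR were not simulated.

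Two stronger readings are not supported. One is that any biasing dropout passes the check unnoticed: level-driven dropout triggers it (row 5), and the failure there lies in the remedy. The other is that the trial's secondary results are biased. Supplementary Table 2 shows 331 of 677 (48.9%) v 576 of 695 (82.9%) participants in the on-treatment set. That is an asymmetry in treatment status, not in missing values, and the documents do not show arm-specific MNAR dropout. The primary outcome is untouched.

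This is a correction that should be made. It does not threaten the trial's main conclusion.

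**What to change.** 1. In SAP 4.4 and protocol 12.8, delete the statements that MAR is tested. In SAP 4.4, also delete the statement that it is ensured.
2. Keep the regression, described as a description of who is missing and a search for auxiliary covariates. Name the visit (3 years) and include treatment arm.
3. Add a delta-adjusted (tipping-point) sensitivity analysis for 3-year eGFR, systolic pressure and ACR. Impute missing 3-year values under MAR, shift them by a delta that may differ by arm, re-estimate the difference, and report the delta at which the conclusion changes. If ACR is transformed, apply delta on the analysis scale.

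The analysis is easy to read. With a fraction p missing in each arm, the difference moves by about p(T)·δ(T) − p(C)·δ(C). At 27.1% missing, a shift of −1 in the spironolactone arm alone moves it by −0.27; at 10% missing, by −0.10.

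The cost is SAP and protocol wording plus one sensitivity analysis, on data already collected, to run and report.

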#### 4.5 HANDLING OUTLIERS

A possible outlier is defined here as a data-point being at least three standard deviations from the mean of its distribution in the variable at that time-point and in relation to previous readings of that measure if appropriate. Potential bivariate or multivariate outliers, such as those identified through differences between baseline and follow-up values, will be flagged for checking and by plotting correlated measures.

Residual outliers (these are observations with residuals of large magnitude i.e. observation's outcome value is unusual conditional on its explanatory variable values) will also be flagged for checking and by plotting the residuals after fitting the regression models. Cook's Distance, leverage and other measures of influential outliers in linear regression models will be examined.

Analysis will proceed by retaining identified outliers including data-point outliers, so long as these values are considered to be plausible. Sensitivity analysis will involve a robust approach in which outliers are excluded by being set to missing. If there is no material difference in conclusions, the analysis retaining outliers will be solely reported.

#### 4.6 HANDLING MULTI-CENTRE/CLUSTERED DATA

Practice will be adjusted for in the final analysis by being included as a fixed effect in the cox proportional hazards model in the analysis of the primary outcome. For the secondary analysis linear mixed models will include a random effect for practice to account for the clustering of patients within practices.

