A further search will be performed, again for the preceding 24 months, to identify patients with one reading in the eGFR range 25-29 ml/min/1.73m^2 (with no eGFR >60 ml/min/1.73m^2 in the last 6 months). Patients identified from these searches will be invited to a screening visit, using the same strategy as described above and, if found to be within the 30-50 ml/min/1.73m^2 range, asked to attend the baseline visit a minimum of 6 weeks later. If the patient's eGFR at this visit is not in the 30-50 ml/min/1.73m^2 range but still within the wider range (25-29 ml/min/1.73m^2) the patient will be asked to return 3 months later for a repeat screening visit. This process will repeat throughout the recruitment period for as long as the patient is willing. The initial screening visit will consist of an informed consent procedure and a single renal profile blood test to encompass potassium levels and eGFR.

Initial calculations showed that, for the average practice, 180 patients are likely to meet Stage 3b CKD criteria. Assuming that around 80% of these patients are eligible and at least 50% of these are willing to take part (based on our experience recruiting to heart failure studies which have a similar age distribution as patients with CKD), then 72 patients may be recruited per practice, requiring 37 practices in total, but increased to 60 to allow for poor recruiting practices, or 15 practices per Townsend quartile of deprivation. To improve the representativeness of the trial population, the number of practices per recruiting centre will be increased to 20 with the intention of reducing these numbers by 50% and giving 30 practices per Townsend quartile of deprivation.

Following analysis of the initial patient recruitment data, 20 practices having mailed-out, the number of practices recruited by the 6 main NSPCR hubs was increased to a minimum of 300, to be initiated in a phased manner.

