## 12.2. Description of Statistical Methods

In accordance with CONSORT guidelines, we will record and report participant flow. Descriptive statistics of recruitment, drop-out, and completeness of interventions will be provided. Baseline variables will be presented by randomised group using frequencies (with percentages) for binary and categorical variables and means (and standard deviations) or medians (with lower and upper quartiles) for continuous variables. There will be no tests of statistical significance nor confidence intervals for differences between groups on any baseline variables.

The primary analysis will be on an intention-to-treat basis. That is, after randomisation, participants will be analysed according to their allocated treatment group irrespective of what treatment they actually receive. The primary outcome will be analysed using a survival analysis method, such as Cox proportional-hazards model, adjusting for practices. Results will be presented as hazard ratios with 95% confidence intervals and associated two-sided P-values. To test the robustness of the result, a sensitivity analysis will be carried out, using the same method, adjusting the following pre-specified baseline prognostic factors: diastolic and/or systolic blood pressure above or below NICE target, type II diabetes and coronary artery disease.

Same approach will be repeated for individual components of the primary composite endpoint and all-cause mortality as secondary analyses. Analyses for other outcomes will be carried out using multiple log-binomial regression models for binary data and linear mixed effect model for continuous data collected over time.

Assumption of proportional hazards will be examined and if any of the assumptions were violated, a suitable alternative survival method will be considered. Similarly, alternative methods will be considered if any violation of assumptions is detected in any of the aforementioned methods for other outcomes.

Adverse effects will be tabulated according to randomised group assignments and the proportions will be compared using Fisher's exact test.

A full detailed analysis plan, including approach of handling missing data, subgroup analyses, and sensitivity analyses, and a plan for interim analysis will be prepared before the final datalock and analysis by a statistician who is independent from the study. All analyses will be performed by the trial statistician and validated by a separate statistician.

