### 2.3 TARGET POPULATION

Eligible patients, from 120 practices recruited by 6 NIHR School for Primary Care Research departments, with previously recorded blood test results suggesting CKD stage 3b will be invited to take part in the trial.

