### 3.5 POOLING OF INVESTIGATIONAL SITES

Data will be collected across all GP practices that randomised patients in the study. These data will be analysed together and GP practice will be included as a random effect in the statistical analysis.

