## 4 PRIMARY ANALYSIS

### 4.1 PRIMARY OUTCOME

The primary analyses will be conducted on all randomised participants, applying the principle of intention-to-treat (ITT), as far as is practically possible, given any missing data. Specifically, the participants will be analysed in the groups to which they were allocated regardless of compliance with the allocated treatment. The primary outcome will be analysed using a mixed effect Cox proportional-hazards method, with a fixed effect for randomised group and practice included as a random effect, with unstructured variance covariance matrix. Results will be presented as a hazard ratio with 95% confidence interval and associated two-sided P-value. A p-value of 0.05 will be used to assess statistical significance. Time to event will be summarised by randomised group using medians and interquartile range.

TABLE 1 DUMMY TABLE FOR PRIMARY OUTCOME

|                    | TREATMENT      |                                  |                  | CONTROL        |                                  |                  | MODEL ESTIMATES |                   |                   |             |
|--------------------|----------------|----------------------------------|------------------|----------------|----------------------------------|------------------|-----------------|-------------------|-------------------|-------------|
|                    | (N=)           |                                  |                  | (N=)           |                                  |                  |                 |                   |                   |             |
|                    | AVAILABLE
N | NUMBER REACHED
ENDPOINT, N(%) | TIME TO
EVENT | AVAILABLE
N | NUMBER REACHED
ENDPOINT, N(%) | TIME TO
EVENT | HAZARD
RATIO | 95%
LOWER C.I. | 95%
UPPER C.I. | P-
VALUE |
| Primary
outcome |                |                                  | Median
(IQR)  |                |                                  | Median
(IQ)   |                 |                   |                   |             |

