#### 4.2.2 THE EFFECT OF ARA IN PATIENTS ON MEASURES OF CARDIOVASCULAR HAEMODYNAMICS

Office measurements of systolic blood pressure (SYSBPR) at baseline, 6 months, 1 year, 2 years and 3 years will be summarised across treatment groups using means and standard deviations. Rates of hypotension (defined in section 2.2.2.1) across the whole study period will be summarised across treatment groups using numbers and proportions of those randomised to each arm. The rates of hypotension across the study period will be analysed by log-binomial regression models and predictors will be treatment allocation and GP practice. The treatment effect will be represented as a relative risk with 95% confidence interval and associated P-value.

The mean change in systolic blood pressure each year from baseline will be analysed with a linear mixed effects model. The model will include systolic blood pressure measurement at each time point and will adjust for baseline measurement and clustering within GP practice will be accounted for as a random effect within the model. An interaction between time and randomised group will be fitted to allow estimation of treatment effect at 6 months and 1, 2 and 3 years. Although 6 months and 1, 2 and 3 years are the main time points of interest, all visits at which BP is recorded will be included in the model to aid estimation of treatment effects in the presence of missing data. The model will also include a patient specific random intercept nested within a practice specific random intercept. Results will be presented as mean difference in change from baseline in systolic blood pressure between the randomised groups at 6 months and 1, 2 and 3 years, with 95% confidence interval and associated 2-sided p value.

The model will include the following fixed effects:

- Time
- Treatment allocation
- Time×treatment allocation
- Baseline systolic blood pressure

The model will include the following random effects:

- GP practice
- Participant ID

The distribution of the change from baseline will be formally assessed for evidence of departure from normality. If necessary, data will either be transformed or analysed using a non-parametric equivalent.

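### SAP 4.6 makes practice a fixed effect in the primary Cox model while SAP 3.5 and 4.1 make it a random effect, so the primary P-value has two definitions, and the fixed-effect one is anti-conservative when practices are many and small

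*Combined protocol and SAP*

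**What the plan says.** Three SAP sections describe how practice enters the primary Cox model.

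- SAP 3.5: "GP practice will be included as a random effect in the statistical analysis".
- SAP 4.1, the section on the primary analysis: a mixed-effect Cox model "with a fixed effect for randomised group and practice included as a random effect, with unstructured variance covariance matrix".
- SAP 4.6: "Practice will be adjusted for in the final analysis by being included as a fixed effect in the cox proportional hazards model". The sentence names the primary outcome, and the next sentence reserves the random effect for the secondary linear mixed models.

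No other section settles the matter. Protocol 12.2 asks for a survival method "such as Cox proportional-hazards model, adjusting for practices" without saying fixed or random. SAP 5.1 and 6.1 say only that practice is adjusted for. The subgroup table in SAP 7 (Table 5) has a hazard-ratio row for practice, which suits a fixed effect. SAP 4.3 makes the secondary analyses follow the primary outcome in how they account for practice, so the ambiguity carries over to them.

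The number of practices is also stated in two ways. Protocol 9.1 reports that after early recruitment data "the number of practices recruited by the 6 main NSPCR hubs was increased to a minimum of 300". Protocol 7.1 and SAP 2 keep a minimum of 120, and SAP 2.3 reads "Eligible patients, from 120 practices recruited by 6 NIHR School for Primary Care Research departments".

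**The concern.** A random practice effect costs one variance parameter. A fixed effect costs one coefficient per practice. With few events per practice, the fixed-effect fit spends a large share of its information on those coefficients. A practice with no event has no finite coefficient and drops out of the fit. In the remaining practices, the many parameters relative to events push the treatment estimate away from zero and make the model-based standard error too small. The two rules are therefore different tests, not two descriptions of one test.

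At stake is the primary P-value. SAP 4.7 makes no multiplicity correction because one hypothesis is tested once, and SAP 4.1 judges that test at 0.05. SAP 2 and 2.5 state that the statisticians know the allocation. With both models written into the plan, a later choice between them could not be shown to be independent of the results.

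**Working it through.** **Inputs from the documents.** Allocation 1:1, randomisation stratified by practice in blocks of varying size, two-sided 5% level, 36 months of follow-up. Planned total 3022, 13.4 events per 100 person-years, HR 0.80, 10% attrition (protocol 12.3). Randomised total 677 + 695 = 1372 (Supplementary Table 2). Its analysis without PAD shows 94 + 96 = 190 events at 5.60 and 5.37 per 100 years, so 5.5 was used.

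**Participants per practice.** 3022/300 = 10.1; 3022/120 = 25.2; 1372/300 = 4.6; 1372/120 = 11.4.

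**The plan's own figure.** Neither document calculates the effect of practice adjustment. The planned total can be reproduced. With 13% withdrawal, HR = 0.8^0.87 = 0.8235. Events = 4(1.96 + 0.842)²/(ln 0.8235)² = 834 (rounded up). Mean 3-year risk = ½[(1 − e^(−0.402)) + (1 − e^(−0.402×0.8235))] = 0.3064. Then 834/(0.3064 × 0.9) = 3024, against the stated 3022. The diluted effect printed in protocol 12.3, 0.84, does not lead to this total; that is a separate matter.

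**Simulation.** No closed formula gives the error of the fixed-effect fit. Trials were simulated with permuted blocks within practice, 3 years of follow-up and 10% attrition. Each data set was analysed by unadjusted Cox, Cox with one coefficient per practice, Cox stratified by practice and, where stated, Cox with a Gaussian practice effect. Assumed, not in the documents: SD of the practice log hazard 0.3 and unequal practice sizes.

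Type I error at nominal 5%:

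| Participants / practices | Runs | Fixed | Unadjusted | Stratified | Random |
|---|---|---|---|---|---|
| 1372 / 300 | 2000 | 8.4% | 4.9% | 5.1% | 5.1% |
| 1372 / 120 | 1500 | 5.8% | 4.3% | 4.0% | not run |
| 3022 / 300 | 2000 | 7.0% | 5.4% | 5.1% | not run |
| 3022 / 120 | 800 | 7.4% | 5.9% | 6.1% | not run |

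The Monte Carlo standard error of the fixed-effect figures is about 0.6 points, or 0.9 for the last row.

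**Cross-check from the standard errors.** If the estimate is centred on zero but its SE is too small, the rejection rate is 2[1 − Φ(1.96 × SE/SD)].

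- 1372/300: SE 0.1538, SD 0.1772, ratio 0.868, giving 8.9%.
- 1372/120: SE 0.1452, SD 0.1513, ratio 0.960, giving 6.0%.
- 3022/300: SE 0.0669, SD 0.0721 (two batches pooled), ratio 0.927, giving 6.9%.
- 3022/120: SE 0.0658, SD 0.0699, ratio 0.941, giving 6.5%.

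These agree with the table within simulation error, so the understated SE accounts for the excess under the null.

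**Information lost.** At 1372/300 with HR 1, about 133 of 300 practices had an event. The fixed-effect fit kept 813 of 1372 participants, and 197 events over 133 practices is 1.5 events per practice coefficient.

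**Estimate at true HR 0.80** (ln 0.80 = −0.223):

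| Participants / practices | Fixed log HR | Unadjusted log HR | Fixed v unadjusted | Fixed v ln 0.80 |
|---|---|---|---|---|
| 1372 / 300 | −0.259 | −0.220 | 18% further | 16% further |
| 1372 / 120 | −0.235 | −0.221 | 6% | 5% |
| 3022 / 300 | −0.228 | −0.210 | 9% | 2% |
| 3022 / 120 | −0.233 | −0.225 | 4% | 4% |

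At 1372/300 the mean HR was 0.772 with fixed and 0.802 with random practice effects.

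**Other assumptions.** With a practice log-hazard variance of 0.05 instead of 0.09 (0.3²), 1372 participants and 300 practices, type I error was 8.0% fixed and 5.6% random (900 null runs, the random effect fitted with its variance known). A separate smaller simulation (400 to 500 runs per setting) gave 7.5% fixed at 300 practices and 6.2% at 120.

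**The case against.** The strongest reply is that SAP 4.1 is the section that defines the primary analysis, gives a full model and agrees with 3.5, so 4.6 is one stray sentence. SAP 1.2 requires deviations to be described and justified, and SAP 9 has the primary analysis validated by a senior statistician or delegate. This makes an undisclosed switch less likely. It does not say which rule is the deviation, and 4.6 is too specific about the primary outcome to pass as loose wording.

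The second reply is that the harm depends on an input that the documents leave open. This stands. With 120 practices and 1372 participants, the 5.8% has an exact 95% interval of 4.7% to 7.1%, which includes 5%. Protocol 9.1 describes a later increase, which favours 300, but no final count is given. Dividing an achieved 1372 by a planned 300 also mixes two sources.

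Four stronger readings are tempting and are not supported:

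- That type I error doubles at the planned size. In 2000 runs it was 7.0%.
- That the fixed effect always inflates the treatment effect. Under HR 1 the estimate stayed centred on 1; the shift arises only when the true HR differs from 1.
- That the log-binomial model for hypotension ("The rates of hypotension across the study period will be analysed by log-binomial regression models and predictors will be treatment allocation and GP practice") cannot be fitted. Practices with no event have no finite coefficient if practice is entered as one coefficient each. However, the section does not say fixed, and 60 trial fits with practice coefficients at an assumed 5% risk all converged with a finite treatment estimate. These outcomes are exploratory (SAP 4.7), and SAP 4.8 allows alternative methods.
- That the trial's primary result was obtained with the fixed effect. The documents do not show which model was used.

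**Conclusion.** The contradiction is explicit and unresolved, and it concerns the only confirmatory test. That part needs no assumption. One of the two rules, followed as written, is anti-conservative: with 1372 participants, type I error is about 8% at 300 practices and about 6% at 120; with 3022 it is about 7%. The cause under the null is a standard error that is too small. When there is a true effect, the log hazard ratio at 1372 participants is also about 6% to 18% further from the null than the unadjusted estimate on the same data.

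The direction is consistent across the settings tried. The sizes rest on an assumed between-practice variance and on 120 or 300 practices. The evidence is clear at 300 practices and weaker at 120. The random effect was checked under the null only at 1372/300, where it held its level.

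The binary outcomes are a secondary point. If hypotension had a 5% risk (an assumption; the documents give none), the share of equal-sized practices with no event would be 0.95^25.2 = 27%, 0.95^11.4 = 56%, 0.95^10 = 60% or 0.95^4.6 = 79%. The practice adjustment should therefore be stated, but failure to converge is not claimed.

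**What to change.** Replace the fixed-effect sentence in SAP 4.6 with the random practice effect of 4.1, and name that as the only primary model. Use the same model in SAP 5.1, 6.1 and 7, and drop the practice row from Table 5. A Cox model stratified by practice matches the randomisation and stayed close to its nominal level in these runs (4.0% to 6.1%), so it could be a named sensitivity analysis.

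For the log-binomial models in SAP 4.2.2, state a practice adjustment that does not use one parameter per practice, for example modified Poisson regression with variance robust to clustering by practice.

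The cost is SAP wording only. If the analysis has already been done, the report should say which model was used and show the other beside it.
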